## Abstract

**Background:**

Suspicious pigmented lesions are a common presenting problem in general practice consultations; while the majority are benign a small minority are melanomas. Differentiating melanomas from other pigmented lesions in primary care is challenging: currently, 95% of all lesions referred to a UK specialist are benign. The MoleMate system is a new diagnostic aid, incorporating a hand-held SIAscopy scanner with a primary care diagnostic algorithm. This trial tests the hypothesis that adding the MoleMate system to current best primary care practice will increase the proportion of appropriate referrals of suspicious pigmented lesions to secondary care compared with current best practice alone.

**Methods/design:**

The MoleMate UK Trial is a primary care based multi-centre randomised controlled trial, with randomisation at patient level using a validated block randomisation method for two age groups (45 years and under; 46 years and over). We aim to recruit adult patients seen in general practice with a pigmented skin lesion that cannot immediately be diagnosed as benign and the patient reassured. The trial has a 'two parallel groups' design, comparing 'best practice' with 'best practice' plus the MoleMate system in the intervention group. The primary outcome is the positive predictive value (PPV) of referral defined as the proportion of referred lesions seen by secondary care experts that are considered 'clinically significant' (i.e. biopsied or monitored). Secondary outcomes include: the sensitivity, specificity and negative predictive value (NPV) of the decision not to refer; clinical outcomes (melanoma thickness, 5 year melanoma incidence and mortality); clinician outcomes (Index of Suspicion, confidence, learning effects); patient outcomes (satisfaction, general and cancer-specific worry), and cost-utility.

**Discussion:**

The MoleMate UK Trial tests a new technology designed to improve the management of suspicious pigmented lesions in primary care. If effective, the MoleMate system could reduce the burden on skin cancer clinics of patients with benign pigmented skin lesions, and improve patient care in general practice.

## Background

### 1.1 Melanoma and health policy

Suspicious pigmented lesions (SPLs), or 'moles' are a common presenting problem in general practice consultations, and while the majority are benign, a small minority are malignant melanomas. Melanoma is a serious skin cancer, accounting for less than one in ten skin cancers, but responsible for 2% of all cancers and 1% of all cancer deaths in the UK, with around 9,500 new cases and 1,800 deaths a year (Cancer Research UK). Worldwide, the incidence of melanoma is increasing faster than any other cancer, with an approximate doubling of rates every 10-20 years in countries with white populations [1]. While the incidence in the UK is one of the highest in Europe, it is lower than the reported incidence from other countries such as Australia and New Zealand, which lead the world age-standardised rates at about 50 per 100,000 population per annum [2] (compared with 11.9 per 100,000 population in the UK (Cancer Research UK)). Furthermore, although the incidence of melanoma increases with age, a third of all cases occur in people aged less than fifty years and it is the second most common cancer in the 20-39 age group. The increasing incidence has been attributed to increases in ultra-violet exposure, both natural and artificial. Other risk factors include genetic predisposition reflected in the phenotypic features of multiple moles, fair complexion, sunburn-susceptible skin types, and family history. In the UK, melanomas are more common in women than in men, although the prognosis is poorer for men over 60 years who tend to present with thicker melanomas [3].

Early detection is critical in reducing mortality and morbidity from melanoma, as thin lesions (Breslow thickness less than 1 mm) have a five-year survival of over 95%, compared to less than 50% for thicker lesions (Breslow thickness more than 4 mm). There is evidence from the UK that expert consultation within 2 weeks of referral results in thinner tumours and improved overall survival [4]. The Department of Health's recent Cancer Reform strategy highlighted the issues of poor public awareness of cancer symptoms, diagnostic delays in primary care and late diagnosis across all cancers. In response, the National Awareness and Early Diagnosis Initiative was jointly launched by Cancer Research UK and the Department of Health in 2008 [5] with two of the seven key objectives being to develop interventions to promote early presentation and reduce diagnostic delays in primary care.

### 1.2 Primary care management of suspicious pigmented lesions

While some patients present late, the vast majority who present to their general practitioners (GPs) with concerns about moles or other pigmented skin lesions, will not be diagnosed with melanoma: even among men aged over 60 years, less than 1 in 33,000 moles are estimated to become malignant [6]. GPs need to be able to reassure those with benign lesions and rapidly refer those with suspicious lesions. This is a difficult challenge and, when compared with dermatologists, GPs can be highly sensitive but less specific for the diagnosis of melanoma [7,8]: consequently, the majority of lesions referred to skin cancer clinics in the UK prove to be benign [9]. Referral or diagnostic efficiency can be measured in terms of the ratio of benign to malignant lesions, or the proportion of referred lesions that are malignant. In 2003, the UK All Party Parliamentary Group on Skin reported that up to nineteen out of every twenty lesions referred to a dermatologist by a GP under the two-week cancer standard were benign. An evaluation of England's 2-week wait referrals showed that melanomas and squamous cell carcinomas accounted for 10 - 12%, with the remainder found to be benign lesions [10].

In an attempt to maximise sensitivity and specificity of melanoma diagnosis by GPs and their referral efficiency, a variety of educational, checklist and technical approaches have been developed. There is equivocal evidence about the usefulness of training courses: while randomised controlled trial evidence from the US suggests some benefit from face-to-face [11] and internet [12] training, Australian studies have shown that face-to-face training of GPs in melanoma diagnosis has no significant effect on their performance [7]. The ABCD [13] and seven-point [14] checklists have been widely evaluated and revised, but each has significant drawbacks in helping GPs distinguish between benign pigmented lesions and melanomas [15]. Technical approaches include the use of dermoscopy, laser microscopy, ultrasonography and magnetic resonance imaging [16]. A recent trial of dermoscopy and digital monitoring in Australian general practice found that the combination of these techniques can increase the sensitivity of GPs for the diagnosis of melanoma, and significantly reduce the proportion of benign lesions excised [17]. However, learning these techniques took considerable time and was completed by only 62% of trial GPs. Therefore, other approaches that are easier to learn are still required to improve GPs' diagnostic performance and support the assessment of pigmented skin lesions in primary care.

### 1.3 SIAscopy and the MoleMate system

SIAscopy is an innovative technology that uses a non-invasive multispectral scanning technique to produce images of the light-absorbing chromaphores haemoglobin, melanin and collagen, in the epidermis and papillary dermis. Patterns within the SIAscans of pigmented skin lesions have been shown to indicate histopathological and pathophysiological features consistent with melanoma, and, in combinations, these features were highly sensitive (83%) and specific (80%) for melanoma in the experimental setting [18]. The Moncrieff Scoring System was developed and, in a population referred to a skin cancer clinic, was shown to have 94.4% sensitivity and a 3.7% false positive rate for melanoma [19]. In the primary care setting the Moncrieff Scoring System was less sensitive for the diagnosis of 'suspicious' lesions (54.2%) and melanoma (66.7%), and a new Primary Care Scoring Algorithm (PCSA) was developed to account for the higher prevalence of seborrhoeic keratoses and haemangiomas seen in primary care. This had a similar sensitivity for the diagnosis of 'suspicious' (50.0%) but was more specific (84.2%). Based on simulation modelling, the PCSA also demonstrated high sensitivity and specificity for the diagnosis of melanoma (94.0% and 83.5% respectively) [20,21].

Subsequently the PCSA was incorporated into the MoleMate system. This randomised controlled trial (RCT), set in UK general practice, aims to test the hypothesis that use of the MoleMate system will improve the management of suspicious pigmented lesions in primary care compared with current best practice, and that this will be reflected in the appropriateness of referrals to skin cancer clinics.

## Methods/designs

### 2.1 Definitions

For the purpose of this trial, the definition of 'suspicious pigmented lesion' is any lesion presented by a patient, or opportunistically seen by a clinician in general practice, which cannot immediately be diagnosed as benign and the patient reassured.

The definition of 'appropriateness of referral' is whether the referred lesion is deemed 'clinically significant' by a dermatologist in a skin cancer clinic and is therefore either biopsied or monitored. Those lesions seen by a dermatologist in a skin cancer clinic which result in reassurance and discharge from the clinic without biopsy or monitoring are deemed 'clinically insignificant'.

### 2.2 Sponsorship and ethical approval

The trial is jointly sponsored by the University of Cambridge and Cambridgeshire Primary Care Trust (now renamed NHS Cambridgeshire). Cambridgeshire 2 Research Ethics Committee has reviewed and approved the protocol (07/H0308/167).

### 2.3 Trial design and randomisation

This randomised controlled trial comprises 2 stages: a pilot phase and the main trial. The pilot phase was conducted in 3 general practices over a 4-month period; during this time the study procedures were refined and projected recruitment rates confirmed. The study design and flow of participants through the trial are shown in Figure 1. Once eligible patients have been internally referred within the general practice to one of the trial Lead Clinicians and recruited into the trial, participants are randomised to either the comparison ('best practice') group or the intervention (MoleMate system) group. Participants are randomised using a block randomisation method with sets of numbered, sealed envelopes prepared by the trial statistician ([name]), with the order of the sequences used being verified afterwards. Randomisation is stratified by age (45 years and under; 46 years and over) and by Lead Clinician.

**Figure 1 F1:**
[figure not shown]
**Trial flowchart**.

### 2.4 Setting

Fifteen general practices are participating in the trial: thirteen in Cambridgeshire, one in West Essex and one in Suffolk. Practices already using a MoleMate system have been excluded. Two Lead Clinicians per practice have undergone training in the use and interpretation of the MoleMate system, and in all study procedures. GPs with known dermatological expertise eg GPs with a special interest (GPSI), Hospital Practitioners and Clinical Assistants in Dermatology, were excluded from being Lead Clinicians.

### 2.5 Patients

Patients are eligible for the trial if aged 18 years or over, able to give informed consent, and have a pigmented lesion (either presented by the patient or noticed by a health care professional) which is not immediately diagnosed as benign and the patient reassured. These patients are given an appointment with a Lead Clinician within one week and provided with information about the MoleMate Trial prior to formal consent and recruitment by the Lead Clinician.

### 2.6 Study procedures

At the trial consultation, the Lead Clinician consents and randomises the patient into the 'comparison' or 'intervention' group.

#### Comparison group

Participants in the comparison group have their lesion assessed in the usual 'best practice' manner using the clinical history, naked eye examination and the seven-point checklist [14].

#### Intervention group

Prior to commencing patient recruitment, Lead Clinicians complete a MoleMate Training CD-rom which teaches users to identify relevant SIAscopic features of various pigmented skin lesions. The Training CD-rom takes up to 2 hours to complete and has been shown to significantly improve GPs' ability to interpret SIAscopic images [22]. Participants in the intervention arm have their lesion/s assessed according to the same 'best practice' principles in the comparison arm. Lead Clinicians then use the MoleMate system to support their assessment and management of the lesion.

For all lesions an Index of Suspicion scale is completed, and the clinical diagnosis and intended action recorded (suspicious and refer via the two-week cancer route, or benign and reassure). A digital photograph is taken of every lesion for expert review.

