### 2.10 Sample size

Our pilot study confirmed projected recruitment rates (6-8 participants per practice per month) and referral rates (approximately 2 referrals per practice per month). Based on these, to detect an increased biopsy rate of 10% amongst those referred of 22% ('intervention' group) versus 12% ('comparison' group), an odds ratio of 2.0, with 80% power at the 5% significance level, would require 442 analysed in the primary outcome sample of referred lesions. With the involvement of 15 practices, this would require 30 referred lesions per practice. Assuming a 25% referral rate this could be achieved by randomising 120 patients per practice (1800 total) with an assumed recruitment rate of 90 per year over a 16-month period.

A blinded interim analysis, presented at the Trial Steering Committee meeting half-way through the study (September 2009) after 747 participants had been randomised, established a lesion referral rate of 28% (254/913), a mean cluster size amongst the referred sample of 1.06 (254 lesions from 239 participants), and that 55% of the referred lesions were assessed by the dermatology experts to be 'clinically significant' in the combined arm data. In this context of a higher rate of biopsy or monitoring, the clinically worthwhile difference was altered to a 15% difference (an odds ratio of 1.8) from 45% to 60%. A target total of 400 referred lesions from approximately 380 patients would provide 80% power to detect this difference at the 5% level of significance, and would require an estimated 1450 study lesions from 1150 randomised participants.

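### The lesions analysed for specificity and NPV are not fixed before allocation, so which lesions are counted can depend on the arm

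*Protocol article*

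**What the plan says.** Section 2.6 gives the order of events: "At the trial consultation, the Lead Clinician consents and randomises the patient into the 'comparison' or 'intervention' group". Assessment is described after that, separately by arm. For the comparison group: "Participants in the comparison group have their lesion assessed in the usual 'best practice' manner". For the intervention group: "Participants in the intervention arm have their lesion/s assessed" by the same principles as in the other arm, followed by "Lead Clinicians then use the MoleMate system to support their assessment and management of the lesion". The clinician who randomises thus also operates the scanner, records the diagnosis and decides on referral, and cannot be blind to the arm.

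Section 2.1 defines a study lesion as one that the patient presents, or that a clinician in general practice notices by chance, and that is not judged benign on sight. Eligibility in section 2.5 is set at patient level and needs one such lesion.

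The units of analysis differ by outcome. The primary PPV uses referred lesions (2.9.1). Sensitivity, specificity and NPV use every lesion in the trial (2.9.2) and follow the primary method, a mixed model with patient as random term (2.11). Referral volume and the melanoma rate are per participant (2.11).

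The blinded interim analysis in section 2.10, after 747 participants, "established a lesion referral rate of 28% (254/913), a mean cluster size amongst the referred sample of 1.06", the last figure being 254 referred lesions from 239 participants. The revised plan expects 1450 lesions from 1150 participants, 400 of them referred.

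**The concern.** Randomisation makes the two groups of patients comparable. It does not do so for a set of lesions chosen within patients after the arm is known. The definition of a study lesion admits a mole first noticed at the trial consultation, and the only filter on it is a judgement by the clinician who already knows the allocation. A scanner at hand could make it more natural to look at, and record, a second mole.

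If one arm records more lesions that are benign and not referred, these add true negatives in that arm only. Specificity and NPV rise there although no referral decision on any other lesion has changed, and the difference could be read as a benefit of the device. The random patient term corrects the standard error for lesions that share a patient. It does not remove an arm difference in which lesions are entered. Section 2.11 says the accuracy data may feed further development of the diagnostic algorithm, so a spurious difference would matter beyond the trial report.

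**Working it through.** **Inputs from section 2.10.** 747 participants, 913 lesions, 254 referred lesions from 239 participants, 55% of referred lesions clinically significant (arms combined); planned 1150 participants, 1450 lesions, 400 referred.

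**The plan's own figures reproduce.** 254/913 = 27.8%, stated as 28%. 254/239 = 1.063, stated as 1.06.

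**How common are multiple lesions?** Interim: 913/747 = 1.22 per participant, so 913 − 747 = 166 lesions beyond one each. Planned: 1450/1150 = 1.26, so 300 beyond one each.

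**Illustration at the planned size.** Per arm: 575 participants, 725 lesions, 200 referred, 525 not referred. At 55%, the referred lesions split into TP = 110 and FP = 90. The share of non-referred lesions that experts would call suspicious is not in the article. I assume 2%, with a range of 1% to 10%. At 2%, FN = 0.02 × 525 = 10.5 and TN = 514.5.

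- Specificity = TN/(TN + FP) = 514.5/604.5 = 85.1%
- NPV = TN/(TN + FN) = 514.5/525 = 98.0%
- Sensitivity = TP/(TP + FN) = 110/120.5 = 91.3%

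Now add lesions to one arm only, all truly non-suspicious and none referred. Only TN changes.

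| Added per participant | Added lesions | Specificity | NPV | Sensitivity | PPV |
|---|---|---|---|---|---|
| 0 | 0 | 514.5/604.5 = 85.1% | 98.0% | 91.3% | 55% |
| 0.10 | 58 | 572.5/662.5 = 86.4% | 572.5/583 = 98.2% | 91.3% | 55% |
| 0.26 | 150 | 664.5/754.5 = 88.1% | 664.5/675 = 98.4% | 91.3% | 55% |

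Over the assumed range of 1% to 10%, the rise in specificity is 1.3 to 1.5 points at 0.10 and 2.9 to 3.4 points at 0.26. Ignoring clustering, the shift at 0.26 corresponds to z of about 1.6.

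**When sensitivity moves.** If the added lesions carry the same 2% suspicious rate, 150 of them add 3 false negatives: 110/123.5 = 89.1%, a fall of 2.2 points. That counts against the arm that adds them.

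**When PPV moves.** Only if added lesions are referred. Ten added referrals that are not clinically significant would give 110/210 = 52.4%, again against the arm that adds them.

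**When nothing moves.** If the added lesions have the same mix of the four cells as the rest, every cell grows by the same factor and all four measures stay put. The shifts above rest on the assumption that added lesions are benign and not referred.

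**Do the interim counts show that extra lesions are lower risk?** No. It is tempting to compare 239/747 = 32.0% of participants with (254 − 239)/166 = 15/166 = 9.0% of extra lesions. But 239 counts participants with any referred lesion, and 15 counts referred lesions beyond the first referred one within a patient, not referrals among the 166. Suppose every lesion is referred independently with p = 254/913 = 0.278. The number of lesions per patient is not given, so two patterns are assumed:

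- 581 patients with one lesion and 166 with two: expected referred participants 581p + 166[1 − (1 − p)²] = 161.6 + 79.5, about 241; surplus 254 − 241.2 = 12.8.
- 621 with one, 86 with two and 40 with three: 172.8 + 41.2 + 25.0, about 239; surplus 15.1.

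Equal risk thus predicts about 239 to 241 referred participants and a surplus of 13 to 15, which is what was seen (239 and 15).

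**The case against.** Much of the case on the other side stands.

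- A reader might infer from 32% against 9% that extra lesions are clearly lower risk. The interim counts fit equal risk just as well, so any shift computed from that 9% is unsupported. Lower risk in lesions noticed by chance is plausible but not shown.
- A reader might take the singular in one arm and the optional plural in the other as two entry rules. They are not evidence of that: the intervention text itself goes on in the singular, and the rules on recording and photography are worded for all lesions.
- A reader might infer that every endpoint is affected. Referral volume and melanoma rate are per participant, and the primary PPV uses referred lesions only.
- The lesion definition excludes a mole judged benign on sight, and section 2.5 applies that test before the Lead Clinician appointment. This limits casual additions. It does not close the route, because a lesion first noticed at the trial consultation can still qualify on the judgement of a clinician who knows the arm.
- A condensed article may leave the order of listing lesions and opening envelopes to the full protocol. That is fair, and a listing rule may exist. The point rests on what the article does state: the order of procedures, a definition that admits lesions noticed by chance, and accuracy measures computed on every lesion.
- No lesion counts by arm are given, so differential entry has not been shown to occur.

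**Conclusion.** The point holds as an open route to bias in the lesion-level secondary outcomes, chiefly specificity and NPV. It is not a demonstrated bias, and the article does not support a claim that the primary PPV is biased. The size is unknown. It is zero if the arms enter equal numbers of lesions or if added lesions resemble the rest. Under the assumptions stated (planned size, 55% PPV, 2% of non-referred lesions suspicious, additions in one arm only, all benign and not referred), specificity would rise by 1.3 points at 0.10 and 3.0 points at 0.26 added lesions per participant, with no device effect. Multiple lesions are common enough for this to be worth closing, and the remedy is cheap, so it should be changed.

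**What to change.** **Patients still to be randomised.** In both arms, number the qualifying lesions on the case report form before the envelope is opened. Base the lesion-level accuracy analyses on these lesions. Report lesions noticed later separately by arm, with the number referred, so that any effect on PPV can be judged. This concerns which lesions are analysed, not how any lesion is handled clinically.

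**Patients already randomised.** Report lesions per participant by arm, and add a sensitivity analysis on the first-recorded lesion. That lesion may itself have been recorded after allocation, so the analysis is informative but not full protection.

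**Cost.** One entry on the form and one analysis rule. Some post-allocation lesions leave the main accuracy analysis; how many, and how many of those are referred, cannot be told from the article. At the interim, 1150 − 747 = 403 participants were still to be randomised under the revised target; the number remaining now is not stated.
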